### **3.5. Sample size calculation**

Calculation of the number of clinical study subjects: As this study is an investigator-initiated clinical trial, the sample size was determined by referencing existing similar studies and clinical experience..

- 1) Level of significance,  $\alpha=0.05$ (two-tailed test)
- 2) Type II error ( $\beta$ ) is set at 0.2, making the power of the test 80%.
- 3) There is no existing study comparing Korean Chuna therapy and usual care for TMJ-related conditions in Korea. Therefore, based on clinical experience and manual therapy studies in China 1-3), the effect size for comparing the mean differences in pain VAS between the two groups is assumed to be at least medium (effect size = 0.7).
- 4) G\*Power 3.1.7 is used to calculate the sample size.

Assuming an effect size of 0.7, 34 subjects per group (a total of 68 subjects) are required. However, since the main analysis will be performed using ANCOVA, adjusting for baseline outcome values, and assuming a correlation value of 0.3 between baseline and the primary endpoint, the sample size is calculated as  $(1 - 0.3 * 0.3) * 68$ , resulting in 62 subjects. Considering a 30% dropout rate during the study, a total of 80 subjects will be recruited, with 40 subjects per group.

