Adverse events are undesirable and unintended signs (e.g., abnormal laboratory findings), symptoms, or diseases that occur after procedures during the clinical study, and they do not necessarily have to be causally related to the procedure. The analysis primarily includes adverse events suspected by the researcher to be related to the treatment, abnormal laboratory values, and the frequency of serious adverse events. Collected safety data are appropriately summarized, with all serious adverse events described narratively. Adverse events are collected through patient symptom reports and researcher observations and are identified by the frequency of adverse events between groups. The researcher will evaluate the causal relationship between each treatment method and the observed adverse events using a six-step scale (1 = definitely related, 2 = probably related, 3 = possibly related, 4 = probably not related, 5 = definitely not related, and 6 = unknown). All side effects will also be classified into three categories according to Spilker's classification method: Mild (1) - not requiring treatment and not significantly interfering with the subject's normal life (function); Moderate (2) - significantly interfering with the subject's normal life (function) and may require treatment, with recovery after treatment; Severe (3) - requiring intensive treatment due to severe adverse events and leaving sequelae.

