- The proportion of patients whose NRS and VAS, indicators of temporomandibular joint pain, fall to less than half of the baseline will be compared and analyzed by time point. Kaplan–Meier survival analysis will be used to measure the time until the recovery of temporomandibular joint pain to less than half after randomization, and the curves will be compared using the log-rank test. A Cox model will be used to calculate the hazard ratio to compare the rate at which temporomandibular joint pain recovers to less than half, and it will also check if the recovery rate differs by subgroup.
- The significance level for all analyses is set at 0.05. All statistical analyses will be performed using the SAS version 9.1.3 statistical package (SAS Institute, Cary, NC, USA), with significance determined at  $p < 0.05$ .

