#### 7.2.1. Precautions During Chuna Therapy

- Anticipated general side effects, such as mobilization or stimulation of soft tissues around the joints following manual therapy, should be explained to the patient before treatment.
- When performing cervical Chuna therapy, (1) minimize the force of rotational techniques, (2) use techniques that induce segmental rotation with minimal vertebral artery pressure, and (3) avoid unnecessary stress on the vertebral artery and other structures to prevent excessive rotational load on the vertebral artery.
- 

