### **7.5. Interpretation Method**

All adverse events reported during the study period are tabulated, and the incidence rate is calculated. The proportion of patients experiencing adverse events in each group is compared using Chi-square test or Fisher's Exact test.

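### Section 7.5 compares safety between arms only by a chi-square or Fisher test, which has low power at 40 per arm unless adverse events are common; a risk difference with 95% CI would say more

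*Protocol*

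**What the plan says.** Section 7.5, which is headed as the interpretation method for safety, has two sentences. The first is descriptive: "All adverse events reported during the study period are tabulated, and the incidence rate is calculated". The second is the between-arm comparison: "The proportion of patients experiencing adverse events in each group is compared using Chi-square test or" Fisher's exact test. Section 6.3.2 sets the threshold: "The significance level for all analyses is set at 0.05". The closing Statistical Analysis Methods section repeats section 6.3 and adds nothing on safety.

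Other safety description is planned. The adverse events text in section 6.2 puts the main weight on events suspected to be treatment-related, abnormal laboratory values and the frequency of serious events. It adds causality and severity grading, and it says: "Collected safety data are appropriately summarized, with all serious adverse events described narratively". Sections 7.6 and 7.7 send serious events to the IRB.

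The sample size in section 3.5 rests on VAS alone. No adverse event rate, precision or power for safety is given anywhere. No confidence interval is named for a between-arm safety difference.

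**The concern.** The protocol has chosen a between-arm safety method, and that method yields a p-value without an effect estimate or a bound. A significance test in a small trial can be non-significant because there is no excess of events, or because there are too few patients to show one, and the p-value does not separate the two. The number of patients was fixed by a VAS effect size, so nothing in the design makes the test informative for event proportions.

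The experimental arm includes cervical techniques, for which section 7.2.1 tells practitioners to "avoid unnecessary stress on the vertebral artery and other structures to prevent excessive rotational load on the vertebral artery". That sentence concerns technique and not analysis, but it shows why readers will want to know how large an excess of events the data leave open.

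There is also a mismatch of focus. Section 6.2 gives most weight to treatment-related and serious events, while 7.5 tests only patients with any adverse event. Background events unrelated to treatment can dilute that comparison.

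**Working it through.** **Inputs from the protocol.** 40 patients per arm, 1:1 (Summary; section 3.5). Level 0.05 for all analyses (section 6.3.2). Section 3.5 specifies a "two-tailed test" for the sample size only; I assume the same for safety. Tests permitted: chi-square or Fisher (section 7.5).

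**Assumed input.** The usual-care (UC) adverse event rate, taken over a range because the protocol gives none. The alternative examined is a doubling under Chuna manual therapy (CMT).

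**Step 1: the plan's own figure.** With effect size 0.7 and two-sided 0.05, the two-sample t test has power 0.7997 at 33 per arm and 0.812 at 34, so the stated 34 per arm (68 in total) is reproduced. The ANCOVA factor gives (1 − 0.3²) × 68 = 61.88, that is 62, as stated. This shows what the 80% power applies to: the VAS comparison, not event proportions.

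**Step 2: power for a doubling.** Power = Σ over (a, b) of Bin(a; 40, p) × Bin(b; 40, 2p) × [test p-value < 0.05], summed over all 41 × 41 tables. Chi-square is Pearson's test without continuity correction.

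| UC rate | CMT rate | Fisher | Chi-square |
|---|---|---|---|
| 5% | 10% | 4% | 15% |
| 10% | 20% | 16% | 25% |
| 15% | 30% | 28% | 37% |
| 20% | 40% | 41% | 50% |
| 25% | 50% | 56% | 65% |
| 30% | 60% | 73% | 80% |
| 40% | 80% | 95% | 97% |

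If chi-square is used only where the expected counts are at least 5, and Fisher otherwise, the first four rows become 5%, 23%, 37% and 50%. Power passes 50% just above a UC rate of 20% for chi-square and between 20% and 25% for Fisher.

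**Step 3: size needed for 80% power.** n per arm = [1.96 √(2p̄(1 − p̄)) + 0.8416 √(p₁(1 − p₁) + p₂(1 − p₂))]² / (p₂ − p₁)². For 10% versus 20%, p̄ = 0.15 and n = (0.990 + 0.421)² / 0.01 = 199. The same formula gives 435, 199, 121, 82, 58 and 42 per arm at UC rates of 5%, 10%, 15%, 20%, 25% and 30%.

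**Step 4: what an interval adds.** Take 8 of 40 CMT patients and 4 of 40 UC patients with an event (illustrative counts).
- Fisher p = 0.35. Chi-square = 80 × (8 × 36 − 4 × 32)² / (40 × 40 × 12 × 68) = 1.57, p = 0.21. Both tests report only non-significance.
- The risk difference is 0.20 − 0.10 = +10 points. The Wilson limits are 0.1050 to 0.3476 (CMT) and 0.0396 to 0.2305 (UC).
- Newcombe lower limit: 0.10 − √((0.20 − 0.1050)² + (0.2305 − 0.10)²) = −0.061.
- Newcombe upper limit: 0.10 + √((0.3476 − 0.20)² + (0.10 − 0.0396)²) = +0.259.

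The interval says directly that an excess of about 26 points has not been excluded. For 4 versus 2 patients it is +5 points (−8.0 to +18.5; Fisher p = 0.68), and for 12 versus 6 it is +15 points (−3.4 to +32.4; Fisher p = 0.18).

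**Step 5: zero events in one arm.** The exact upper limit for 0 of 40 is 1 − 0.025^(1/40) = 8.8% (two-sided 95%). This bounds the rate in that arm, not the excess between arms.

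**The case against.** Five things can be said for the plan.

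1. Chi-square or Fisher on event proportions is a standard and valid choice, and low power for adverse events is inherent in an 80-patient trial. This stands. The test is not wrong; it is a weak sole summary of the between-arm comparison.

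2. A reader might infer that the protocol will treat p > 0.05 as proof of equal safety. The text does not support this: 7.5 says only that proportions are compared, the stated objective is effectiveness and cost-effectiveness, and no equivalence or non-inferiority claim on safety is made. It follows that no margin is missing, and none is asked for here.

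3. A reader might infer that safety is judged by the p-value alone. That is also too strong. Tabulation, incidence, causality and severity grading, narratives and IRB review of serious events are all planned, and for rare serious harms they matter more than any between-arm test. The word only applies to between-arm inference.

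4. A reader might infer that a doubling is missed most of the time. This depends on a rate the protocol does not give. At a UC rate of 25% both tests detect a doubling more often than they miss it. Quoting Fisher alone would also understate the power, because at 20% versus 40% the expected counts are ample and chi-square would ordinarily be used.

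5. An interval can be computed from the tabulated counts, and a separate SAP, not seen here, may specify one. This lowers the weight of the point but does not remove it. The protocol names its method for interpreting safety, and the criticism is of that choice.

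**Conclusion.** The point holds in a limited form. The only between-arm safety inference is a test on any adverse event at 0.05 with 40 per arm. For assumed UC rates of 5% to 20%, its power to detect a doubling is 4% to 41% by Fisher and 15% to 50% by chi-square. Over that range a non-significant result would say little about excess harm. If events are more common the test does better, with 56% and 65% power at a rate of 25%.

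These figures rest on the assumed rates, a two-sided test and all 40 patients per arm being evaluable. If only 28 per arm contributed (the protocol's 30% dropout), Fisher power at 5%, 10%, 15% and 20% would be 2%, 8%, 17% and 28%.

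Nothing in the section is misstated or contradictory. This is a cheap improvement to a stated method.

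**What to change.** In section 7.5, and in the closing Statistical Analysis Methods section if safety is added there:

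- Make the between-group safety result the risk difference (CMT minus UC) with its 95% CI, and name the interval method (for example Newcombe).
- Report it for any, treatment-related and serious events, so that the table matches the emphasis in section 6.2.
- Give each arm's proportion with an exact 95% CI.
- Keep the chi-square or Fisher p-value as descriptive.
- State that a non-significant test is not evidence of equal safety.

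The cost is a wording change and one extra line per safety table. No additional patients, visits or data are needed. The downside is that the intervals will be wide and the safety statement will read less favourably than a bare non-significant p-value.

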### **7.6. Reporting Method**

- Clinical researchers at each institution must explain all possible adverse events to co-researchers, subjects, or guardians and educate them to report any phenomena observed after the procedure. All local, systemic, or clinical pathology symptoms observed post-procedure must be recorded and stored in the case report form according to clinical research management standards. The principal investigator at each institution must describe and evaluate all symptoms during the clinical study in the clinical research result report. In the event of a "serious adverse event," it must be reported to the Institutional Review Board (IRB) and the principal clinical research institution (Kyung Hee University Korean Medicine Hospital) to determine whether to continue or discontinue the study.
- Additional safety information must be reported periodically until the adverse event is resolved (e.g., disappearance of the event or impossibility of follow-up). The principal investigator at each institution must conduct all aspects of the clinical study in accordance with the Declaration of Helsinki.

### **7.7. Reporting of Serious Adverse Events**

- The clinical study principal investigator and personnel must ensure the safety of subjects and take immediate and appropriate action to minimize adverse events in the event of serious adverse events.
- Duties of each responsible party in the event of a "serious adverse event" during the clinical study:
  1. **Principal Investigator's Duty** The principal investigator must immediately report the serious adverse event to the IRB and suspend part or all of the clinical study until further instructions are received.
  2. **Clinical Researcher's Duty** Clinical researchers must immediately report any serious adverse events to the principal investigator and the IRB.
  3. **IRB's Duty** The IRB must decide whether to continue or discontinue part or all of the clinical study in the event of a serious adverse event and issue necessary instructions, such as suspension, to the principal investigator.
  4. **Sponsor's Duty** The sponsor must immediately notify all relevant institutions upon receiving reports of serious and unexpected adverse events from the principal investigators or clinical researchers.

## **8. Safety Monitoring Plan and Data Safety Monitoring Plan**

Ensuring Subject Safety and Data Integrity: The plan includes a review of subject safety and a comparison of case report forms with source documents to ensure data completeness.

Monitoring Schedule: Monitoring will be conducted three times: an initial monitoring at the start of subject enrollment, one interim monitoring during the clinical study, and a final monitoring at the study's completion. The monitoring will be carried out by the monitoring staff of the Jaseng Medical Foundation Spine & Joint Research Institute.

## **9. Subject Information and Consent Forms**

Individual Written Consent: All patients must provide written consent, which includes the purpose of the study, procedures, countermeasures in case of adverse events, and data privacy protection measures. The consent form provided as an appendix will be used.

Explanation and Consent Forms: The subject information and consent forms follow the templates provided in the appendix.

## **10. Measures for Subject Safety and Compensation Protocol for Victims**

### **10.1. Confidentiality of Study Subjects**

All personal information of study subjects will be strictly managed under the supervision of the Institutional Review Board (IRB). The confidentiality and protection of the personal information of study subjects will be maintained. All data collected from subjects who agree to participate in this study will be anonymized and may be provided to other institutions with anonymous codes for research purposes, excluding personal information.

## **10.2. Other Necessary Measures for Safe and Scientific Conduct of Clinical Studies**

In case of direct injury related to the study, appropriate medical treatment will be provided as determined by the clinical study investigator, and compensation for damages will follow the pre-designated study-related insurance terms. Study subjects will be provided with an emergency contact number to reach the principal investigator or study staff if they have any questions, experience medical problems, or suffer study-related illnesses during the study period.

## **11. Recruitment of Study Subjects**

Recruitment Methods: Study subjects will be recruited through press releases about the study, promotional posters inside and outside the clinical study institutions, and free magazine advertisements.

Promotional Posters: Promotional posters will follow the format provided in the appendix.

## **12. Case Report Forms**

This study will follow the template of the 'Case Report Form for the Efficacy and Cost-Effectiveness Evaluation of Chuna Therapy for Temporomandibular Joint Disorders: A Randomized, Controlled, Multicenter Clinical Study' provided in the appendix.

## **13. Timeline**

IRB Approval Plan Submission: June 2018

First Patient Treatment Start: After IRB approval

Last Patient Treatment Start: To be scheduled

Last Patient Follow-Up: To be scheduled

Data Collection Completion: To be scheduled

Analysis: To be scheduled

Report: To be scheduled

## **14. Ethical Considerations**

### **14.1. Compliance with Laws and Regulations**

This clinical study will be conducted in accordance with the Declaration of Helsinki and its latest amendments and/or all relevant regulations, following Good Clinical Practice (GCP) guidelines.

### **14.2. Informed Consent of Clinical Study Subjects**

Before starting the clinical study, subjects will be thoroughly informed about the study's content and treatment methods (including efficacy, adverse reactions, and safety) and will be required to sign a consent form voluntarily. Only after obtaining the signed consent form can subjects participate in the clinical study, and a copy of the consent form will be provided to them.

### **14.3. Institutional Review Board (IRB)**

IRB Submission: Before the start of the clinical study, the principal investigator must submit the clinical study protocol, informed consent form (ICF), and all relevant information to the IRB/EC for review and approval. All patient recruitment materials must also be approved by the IRB/EC.

Ongoing Reporting: The principal investigator must provide summary updates of the clinical study status to the IRB/EC annually or more frequently if required by the IRB/EC's conditions, policies, and procedures. Any protocol amendments must also be reported to the IRB/EC immediately.

Serious Adverse Event Reporting: Investigators must comply with the IRB/EC's requirements for reporting serious adverse events. Investigators may also receive other safety-related communications. They are responsible for ensuring that these reports are reviewed and processed in accordance with local health authority requirements and IRB/EC policies and procedures, and that they are kept in the clinical study site file.

### **14.4. Compensation for Injury**

Refer to the attached compensation protocol for victims.

### **14.5. Confidentiality**

Unique Identification Numbers: The sponsor will assign unique identification numbers to patients enrolled in the clinical study to maintain confidentiality. This means patient names will not be included in the data provided to the sponsor.

Medical Information Confidentiality: Patient medical information collected during this clinical study is

confidential and, except as permitted or required by law, will be disclosed to third parties only as allowed in the signed consent form (or separate authorization for the use and disclosure of personal health information).

Medical Information Disclosure: Medical information may be provided to appropriate medical personnel for treatment purposes.

Data Use: Data from this clinical study may be used for monitoring and investigation by the sponsor's monitors and representatives, and by the clinical study site's IRB/EC as required.

## **15. Management of Clinical Study Documents and Administrative Procedures**

### **15.1. Data Storage and Disposal**

A designated location for storing materials and records related to the conduct of the clinical study will be prepared to ensure security. After the completion of the final report, a custodian will be designated to store clinical study-related documents for three years from the study completion date. Copies of case report forms and other data collected during the study must be submitted to Kyung Hee University Korean Medicine Hospital within one month of study completion, while the originals will be stored separately according to the institution's IRB regulations. Records and documents will be shredded to prevent information leaks once the storage period has expired, and personal information will be destroyed in accordance with Article 16 of the Personal Information Protection Act Enforcement Decree.

### **15.2. Deviation from the Clinical Study Protocol**

Investigators and staff must fully understand and strictly adhere to the protocol to prevent violations. To comply with the visit schedule, the staff must take appropriate actions, such as providing written notifications or conducting telephone monitoring for the next visit time. In case of unavoidable protocol violations, the following procedures will apply:

Serious Protocol Violations: For significant violations such as subject withdrawal/drop-out criteria, subject inclusion/exclusion criteria violations, failure to obtain consent, or mid-study drop-out criteria, subjects may be dropped from the study after consultation with the investigator.

Minor Violations: Minor violations must be accurately recorded along with the reasons and extent of the delay, and their impact on the clinical study will be considered during the result analysis.

### **15.3. Data Publication and Protection of Trade Secrets**

The sponsor may provide information about the clinical study publicly to medical professionals and the public through conferences and publications, and must comply with all requirements for publishing clinical study results. Study results may not be published or used in part or whole without the consent of the principal institution, Kyung Hee University Korean Medicine Hospital.

### **15.4. Protocol Amendments**

If protocol changes are necessary, the sponsor will prepare a protocol amendment. Except for changes required to eliminate immediate hazards to subjects or administrative changes, all amendments must receive IRB/EC approval before implementation.

# Statistical Analysis Methods

## 1. Statistical Analysis

- This study is a randomized controlled trial of Chuna manual therapy for patients with temporomandibular joint pain, comparing the differences within and between groups based on effectiveness.

